## Abstract

**Background:**

Evidence on the effectiveness of intra-articular corticosteroid injection for hip osteoarthritis is limited and conflicting. The primary objective of the Hip Injection Trial (HIT) is to compare pain intensity over 6 months, in people with hip OA between those receiving an ultrasound-guided intra-articular hip injection of corticosteroid with 1% lidocaine hydrochloride plus best current treatment with those receiving best current treatment alone. Secondary objectives are to determine specified comparative clinical and cost-effectiveness outcomes, and to explore, in a linked qualitative study, the lived experiences of patients with hip OA and experiences and impact of, ultrasound-guided intra-articular hip injection.

**Methods:**

The HIT trial is a pragmatic, three-parallel group, single-blind, superiority, randomised controlled trial in patients with painful hip OA with a linked qualitative study. The current protocol is described, in addition to details and rationale for amendments since trial registration. 204 patients with moderate-to-severe hip OA will be recruited. Participants are randomised on an equal basis (1:1:1 ratio) to one of three interventions: (1) best current treatment, (2) best current treatment plus ultrasound-guided intra-articular hip injection of corticosteroid (triamcinolone acetonide 40 mg) with 1% lidocaine hydrochloride, or (3) best current treatment plus an ultrasound-guided intra-articular hip injection of 1% lidocaine hydrochloride alone. The primary endpoint is patient-reported hip pain intensity across 2 weeks, 2 months, 4 months and 6 months post-randomisation. Recruitment is over 29 months with a 6-month follow-up period. To address the primary objective, the analysis will compare participants’ ‘average’ follow-up pain NRS scores, based on a random effects linear repeated-measures model. Data on adverse events are collected and reported in accordance with national guidance and reviewed by external monitoring committees. Individual semi-structured interviews are being conducted with up to 30 trial participants across all three arms of the trial.

**Discussion:**

To ensure healthcare services improve outcomes for patients, we need to ensure there is a robust and appropriate evidence-base to support clinical decision making. The HIT trial will answer important questions regarding the clinical and cost-effectiveness of intra-articular corticosteroid injections.

**Trial registration:**

ISRCTN: 50550256, 28th July 2015.

## Background

Hip osteoarthritis affects a substantial, and growing, number of people worldwide. Its incidence and prevalence are increasing due to ageing and obesity. It is estimated that between 10 and 18% of those aged over 60 years are affected, rising to one in three patients over the age of 85 years [1], with a substantial proportion experiencing persistent pain, loss of function and decline in health-related quality of life [2].

In 2016, in the United Kingdom (UK), an estimated 92,465 primary total hip replacement (THR) operations were carried out, with approximately 90% being performed for OA [3]. Whilst not all patients with hip osteoarthritis will need a THR, the numbers of THR are continuing to rise [4, 5]. Patients with hip OA are typically treated in primary care for several years before referral for surgical opinion, with evidence suggesting that primary care management is suboptimal and that patients with hip pain feel their pain is neglected despite consulting their general practitioner (GP) [6]. In one observational study from the Netherlands, patients with incident hip OA remained under GP care for an average of 7 years (82 months) before referral to orthopaedics, suggesting that a considerable period of time is available to help patients through the application of non-surgical interventions before surgery is suggested as an option [7]. This is important, as non-surgical interventions could significantly contribute to postponing hip replacement [8], which in turn can delay or prevent future revision surgery.

A range of treatments, including analgesia and exercise therapy, are available to help people with hip OA, although the evidence supporting their use, especially in primary care settings, is limited. Influential organisations including the European League Against Rheumatism (EULAR), Arthritis Research UK and the National Institute for Health and Care Excellence (NICE) highlight the lack of evidence from randomised controlled trials (RCTs) conducted exclusively with people with hip OA [9, 10]. NICE guidance for the non-surgical treatment of OA advises a combination of non-pharmacological and pharmacological treatments, with education, exercise and weight reduction being core treatments [9]. Options for analgesia include paracetamol, oral non-steroidal anti-inflammatory drugs (NSAIDs) and opiates, with intra-articular corticosteroid injection recommended as an adjunct for those with moderate-severe pain.

Intra-articular corticosteroid injection is not used to treat patients with hip OA as widely as it could be in the UK owing to a lack of local availability and uncertainties about patient selection and potential benefit [11]. Intra-articular hip injection is typically administered using imaging guidance, either fluoroscopy or ultrasound, to improve the accuracy of the injection [12]. The evidence supporting the use of intra-articular corticosteroid injection for hip OA is limited and conflicting. Of the five published RCTs of intra-articular corticosteroid injection for hip OA [11, 13–16], all recruited small numbers of participants from secondary care (≤40 per treatment group) and employed short-term follow-up (maximum three months). Whereas two RCTs with hip OA patients have demonstrated clinical benefits at eight weeks post-injection [11, 16] and two at three months [14, 16], one reported no significant difference in pain or function at three months [15]. There is evidence that beneficial effects of knee injections persist to six months [17]. All previous RCTs of corticosteroid injections for hip OA have included a ‘placebo’ arm of injections of either local anaesthetic or saline but only one has compared clinical effectiveness of corticosteroid injection with best usual care [11].

There is, therefore, promising evidence to support the use of intra-articular corticosteroid injection for patients with hip OA, although current research is restricted to small studies of more severely affected patients with only short-term follow-up. The available studies therefore do not reflect the true range of disease managed in primary care, where patients may have less severe disease and are more likely to have multi-morbidity which limits their other treatment options. To ensure healthcare services improve outcomes for patients we need to ensure there is a robust and appropriate evidence-base to support clinical decision making.

## Objectives

The current protocol (version 6.0, 3 April 2018) is described below. Key amendments to the protocol since trial registration are highlighted with comments in square brackets and described in detail, along with rationale for change, in Table 1.

**Table 1 Tab1:** Key Protocol Amendments since Trial registration

Protocol Section	Original protocol	Amended details	Date of Amendment REC approval	Rationale for amendment
Secondary objectives	To explore reasons for non-participation in the study and perceptions of recruitment processes with aim of identifying any modifiable barriers to recruitment [To undertake only if recruitment less than anticipated at 3 month review]	Objective removed	May 2018	We could not to complete the qualitative objective - to explore reasons for non-adherence - due to low recruitment to this qualitative study of people who were eligible for the trial but unwilling to participate. Furthermore, we had identified key modifiable issues to facilitate method of recruitment relating to eligibility criteria (see below) and recruitment route (see ‘Progress of the trial’).
Inclusion Criteria	Moderate-to-severe hip pain (a score of four or more on a 0–10 numeric rating scale (NRS)) on the day of assessment	Moderate-to-severe hip pain (a score of four or more on a 0–10 numeric rating scale (NRS)) on average over the last 2 weeks and current hip pain rated as at least 1 out of 10 (on a 0–10 NRS) on the day of assessment	September 2016	During the first 5 months of recruitment we observed that, due to the day-to day variability of osteoarthritis symptoms, a number of potential participants did not meet the eligibility criterion of pain of 4/10 on the day of assessment.
Exclusion Criteria	Any contraindications to the use of 1% lidocaine hydrochloride as listed in Summary of Product Characteristics (SPC) e.g. complete heart block, hypovolaemia,	Any contraindications to the use of 1% lidocaine hydrochloride as listed in Summary of Product Characteristics (SPC) e.g. complete heart block, hypovolaemia, porphyria	September 2016	A review of the summary of product characteristics (SPC) for lidocaine hydrochloride revealed a new contraindication (porphyria). Porphyria was added to the exclusion criteria as part of an urgent safety measure and subsequent amendment.
	Receiving anticoagulants (warfarin, dabigatran, rivaroxaban, apixaban or low molecular weight heparin)	Receiving anticoagulants (warfarin, dabigatran, rivaroxaban, apixaban or low molecular weight heparin), ritonavir or cobicistat	January 2017	It was noted in the MHRA Drug Safety Update dated 14 December 2016 ‘Cobicistat, ritonavir and coadministration with a steroid: risk of systemic corticosteroid adverse effects’ that coadministration of corticosteroids, including intra-articular triamcinolone, with an HIV-treatment-boosting agent may increase the risk of corticosteroid side-effects including adrenal insufficiency, adrenal suppression and Cushing’s syndrome, due to a pharmacokinetic interaction. Receiving cobicistat or ritonavir were added to the exclusion criteria as part of an urgent safety measure and subsequent amendment.
Sample Size	To address the primary objective, the analysis will be based on comparisons of participants’ ‘average’ follow-up pain NRS scores, based on a random effects linear repeated-measures model, with a ‘cluster’ size of 4 (denoting 4 follow-up assessments) and a postulated coefficient of 0.5. A sample size of 232 will provide 90% power (5% two-tailed significance) to detect a minimum difference of 1.5 points in mean pain NRS score (anticipated baseline SD of pain scores = 4.5 points; effect size of 0.33) between I1 and I2 across the 6-month follow-up period, allowing for total of 15% loss to follow-up. As our trial also evaluates I3 (against I1), we have three groups of interest and hence need 348 participants.	To address the primary objective, the analysis will be based on comparisons of participants’ ‘average’ follow-up pain NRS scores, based on a random effects linear repeated-measures model, with four follow-ups and postulated correlations of 0.5 for repeat-measures and 0.2 for baseline-outcome. A sample size of 136 (68 per arm) provides 80% power (5% two-tailed significance) to detect a minimum difference of 1 point in mean pain NRS score (anticipated SD of about 2.5; effect size of 0.4) between I1 and I2 across the 6-month follow-up period, allowing for 15% loss to follow-up. As the trial also evaluates I3 (against I1), there are three groups of interest and hence 204 participants are needed.	May 2018	The Data Monitoring Committee noted poor recruitment and suggested rerunning the sample size calculations to ensure the original sample size assumptions were still valid. The observed baseline standard deviation (SD) of the primary outcome based on data collected from participants recruited by this time point (n = 65) was 1.7 (and the SD for follow up scores was around 2.5) – i.e. much lower than the SD of 4.5 expected before the start of recruitment on which the original sample size calculation was based. The clinically important difference of 1.5 (originally stated) in the context of this baseline SD would be ‘large’ (effect size above 0.8). The clinically important difference of 1.5 was considered to be too large in relation to the lower expected SD. The clinically important difference for the NRS-pain scale has taken different values across studies; an absolute difference of 1 has been specified in some studies (which would relate to a “moderate” effect size (0.5) when the SD is around 2; or, 0.4 in relation to higher SD of 2.5 which is observed across follow up time points). Hence, we felt that a revised effect size of 0.4 is justifiable. Using this revised effect size of 0.4 and revised power of 80% (on the advice of the TSC), the sample size was amended as described, and was approved by the funder, TMC and DMC.
Recruitment period	The monthly target for recruitment will be 20. A recruitment period of 18 months will therefore be required.	An amended recruitment period of 29 months is required to meet the revised sample size (*n* = 204). The monthly target for recruitment has been adjusted from 20 to 10.	May 2018	During the first 18 months of trial recruitment an average of 7 patients per month were recruited. Recruitment improved since greater emphasis has been placed on recruitment route 3 to an average of 10 per month. Recruitment period was recalculated based on observed recruitment and revised sample size.

### Primary objective

The primary objective of this trial is:To compare longitudinal pain scores over 6 months, in people with hip OA, between those receiving an ultrasound-guided intra-articular hip injection of corticosteroid with 1% lidocaine hydrochloride plus best current treatment with those receiving best current treatment alone.

### Secondary objectives

The secondary objectives of this trial are:To compare the clinical effectiveness of an ultrasound-guided intra-articular hip injection of corticosteroid and 1% lidocaine hydrochloride and best current treatment with best current treatment alone across a range of secondary outcome measures including physical function, stiffness, patient global impression of change, general health, sleep, self-efficacy, and satisfaction with treatmentTo compare the effect of an ultrasound-guided injection of corticosteroid and 1% lidocaine hydrochloride plus best current treatment with an ultrasound-guided injection of 1% lidocaine hydrochloride plus best current treatment on pain, physical function, stiffness, patient global impression of change, general health, sleep, self-efficacy, and satisfaction with treatmentTo compare the cost-effectiveness of ultrasound-guided intra-articular injection of corticosteroid and 1% lidocaine hydrochloride and best current treatment with best current treatment alone over 6 monthsTo explore in a linked qualitative study, the acceptability to, and impact of, ultrasound-guided intra-articular joint injection to patients with hip OATo explore in a linked qualitative study, the experiences of patients of living with hip OATo explore reasons for non-participation in the study and perceptions of recruitment processes with aim of identifying any modifiable barriers to recruitment (to undertake only if recruitment less than anticipated at 3 month review). [Amended, see Table 1]

## Methods

### Trial design

The trial is a pragmatic, three-parallel group, single-blind, superiority, randomised controlled trial in patients with painful hip OA. The intervention arms are:best current treatment (intervention arm 1, I1)best current treatment plus ultrasound-guided intra-articular hip injection of corticosteroid (triamcinolone acetonide 40 mg) and 1% lidocaine hydrochloride (intervention arm 2, I2)best current treatment plus ultrasound-guided intra-articular hip injection of 1% lidocaine hydrochloride alone (intervention arm 3, I3)

Participants with moderate-to-severe hip OA consulting at musculoskeletal clinics at the primary-secondary care interface and in secondary care or identified from a Read Code search at participating General Practices are randomised on an equal basis (1:1:1 ratio) to one of these intervention arms. Follow-up data are gathered from participants at 2 weeks, 2 months, 4 months and 6 months via postal questionnaires. The experience and impact and perceptions of receiving an intra-articular hip injection for hip OA compared to best current treatment alone are explored in in-depth qualitative interviews in a purposive sample of approximately 30 participants (*n* = 10 from each of the three arms of the trial).

### Study setting

Participants are recruited from primary care referrals to orthopaedics, rheumatology and two musculoskeletal National Health Service (NHS) interface services in Staffordshire, UK. These services are variously staffed by GPs with specialist musculoskeletal interests, extended-scope physiotherapists, rehabilitation medicine specialists, rheumatologists and orthopaedic surgeons. The musculoskeletal hip clinics, where patients are screened, consented and treated, take place at the two musculoskeletal interface services in Staffordshire.

The research sites received local management approval, trial specific training covering the interventions (with competency in delivery of the trial interventions being confirmed) and trial administrative procedures, and undertook sufficient research preparation (including Good Clinical Practice (GCP) training) prior to the start of recruitment into the trial.

### Participants

The study population consists of participants with moderate-severe pain attributable to hip OA. Diagnosis is based on presenting symptoms and routine clinical history and examination supported by radiographic evidence of hip OA.

#### Inclusion criteria

Male or female aged ≥40 yearsA clinical diagnosis of unilateral or bilateral hip OA, and confirmed on plain radiography within the last 24 monthsModerate-to-severe hip pain (a score of four or more on a 0–10 numeric rating scale (NRS)) on average over the last 2 weeks and current hip pain rated as at least 1 out of 10 (on a 0–10 NRS) on the day of assessment [amended, see Table 1]Symptom duration of episode of at least 6 weeksHip pain occurring on most days of the last month [18]Informed written consent provided by the patient

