#### Primary outcome measure

Patient-reported hip pain intensity measured using a 0–10 Pain Numeric Rating Scale for current hip pain (hip pain today) [20].

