#### Secondary outcome measures

The secondary outcomes include pain, stiffness and everyday physical function (Western Ontario and McMaster University Arthritis Index (WOMAC v 3.1)) [21], participants’ self-reported global impression of change [22], general health (SF-12, EQ-5D-5 L) [23, 24], sleep disturbance (adapted from Dawson et al. [25]), pain self-efficacy [26], illness perceptions [27], maintenance of and return to desired activities including work and social life, healthcare utilisation including medication use and participant incurred cost, treatments received (including referral for surgery and analgesia), participants’ satisfaction with treatment, work (employment status, performance, absence), joint replacement surgery (National Joint Register). Table 2 summarises the content of the participant questionnaires.

**Table 2 Tab2:** Participant Questionnaire Content

Visits	Baseline	2-week	2-month	4-month	6-month
Baseline measures					
Demographics (date of birth, gender)	✓	✓	✓	✓	✓
Demographics (marital status)	✓				
Hip pain questions: uni/bilateral, duration	✓				
Previous hip injection	✓				
Participant treatment preference and expectations	✓				
Comorbidity	✓				
Self-reported height and weight (BMI)	✓				✓
Other musculoskeletal pain (Body manikin) [22]	✓				
Anxiety and Depression – GAD and PHQ8 [23, 24]	✓				
Primary Outcome measure					
Pain - Numerical Rating Scale score for current pain [20]	✓	✓	✓	✓	✓
Secondary outcome measures					
Function - Western Ontario and McMaster University Arthritis Index (WOMAC v3.1) [32]	✓		✓	✓	✓
Participant’ self-reported global impression of change [33]		✓	✓	✓	✓
General health (SF-12) [34]	✓		✓	✓	✓
Sleep disturbance (Likert type scale, adapted from Dawson et al. [35])	✓		✓	✓	✓
Pain self-efficacy [36]	✓		✓	✓	✓
Modified Brief Illness Perceptions Questionnaire [37]	✓		✓		✓
Satisfaction and experience			✓		✓
Health Economic Outcomes					
Health status - EQ5D-5 L [38]	✓	✓	✓	✓	✓
Employment status	✓				✓
Performance at work	✓		✓		✓
Absenteeism from work	✓		✓		✓
Health care utilisation			✓		✓
Participant -incurred costs			✓		✓
Process Data					
Other hip injections received			✓		✓
Self-reported adverse events		✓	✓		
Adherence to best current treatment advice			✓	✓	✓

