### Sample size

To address the objectives of the trial, 204 participants (68 in each arm) need to be recruited over a 29-month period [amended since trial registration, see Table 1 and ‘Progress of trial’]. To address the primary objective, the analysis will be based on comparisons of participants’ ‘average’ follow-up pain NRS scores, based on a random effects linear repeated-measures model, with four follow-ups and postulated correlations of 0.5 for repeat-measures and 0.2 for baseline-outcome. A sample size of 136 (68 per arm) provides 80% power (5% two-tailed significance) to detect a minimum difference of 1 point in mean pain NRS score (anticipated SD of about 2.5; effect size of 0.4) between I1 and I2 across the 6-month follow-up period, allowing for 15% loss to follow-up. As the trial also evaluates I3 (against I1), there are three groups of interest and hence 204 participants are needed.

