The secondary clinical evaluations will include: evaluation of pain NRS score differences between groups at each of the individual time points (2 weeks, 2 months, 4 months and 6 months) as well as between-group comparison of secondary outcome measures over the 6-month follow-up period. Mixed models for repeated measures (MMRM) will be through linear-regression in respect of numerical outcomes, and logistic-regression in relation to categorical outcome measures. A number of follow-up data are anticipated to be retrieved through minimum data collection, and therefore we will use multiple imputation (MI) using chain equations [26] to impute missing secondary outcome data – the prediction models will include baseline variables and the (primary) pain outcome measure as predictors. MI, similar to mixed modelling, estimates effect on the basis of an MAR missingness mechanism. Estimation of the primary outcome measure based on MI evaluation will be carried out as a sensitivity analysis of the main MMRM analysis. In addition, an MI analysis incorporating plausible deviations from ignorable missingness will be considered in respect of sensitivity analysis of the primary outcome to MNAR missing data.

The primary analyses will be adjusted for the following baseline covariates: pain score, age and gender (and EQ5D for health economic evaluation). Estimates of clinical effect will be shown as mean (SDs) differences (for numerical outcomes) and odds ratios (for dichotomous outcomes), with 95% confidence intervals (CI). As previously stated, regression analysis will be based on a linear model for numerical outcomes and binary logistic model for dichotomous outcomes with a random-effects component being added to the model for repeated measures data, to take into account the intra-cluster correlation. To help in interpreting the size of the estimated clinical effect for the between-group difference in pain (overall and at individual time points) we will calculate the standardised mean difference (‘effect size’) which is the ratio of the estimated mean difference to the standard deviation of pain scores in the total randomised population. For all evaluations of the primary outcome, we will present mean and 95% confidence interval estimates. The number needed to treat (NNT) with 95% CI will be calculated in respect of the comparison between best current treatment plus corticosteroid and 1% lidocaine hydrochloride injection and best current treatment alone [27].

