#### Progress of the trial

Recruitment commenced in January 2016. Unfortunately, review of recruitment 3–6 months into the trial revealed that recruitment was sub-optimal and less than 50% of that predicted. Two key amendments were made (detailed in Table 1).

First on 19th August 2016 the eligibility criteria were amended. Criterion 3 was originally ‘Moderate-to-severe hip pain (a score of four or more on a 0-10 numeric rating scale (NRS)) on the day of assessment’. During the first 5 months of recruitment we observed that, due to the day-to day variability of osteoarthritis symptoms, a number of potential participants did not meet the eligibility criteria of pain of 4/10 on the day of assessment. The TSC suggested amending the criterion to ‘moderate to severe hip pain (a score of four or more on a 0-10 numeric rating scale (NRS)) on average over the last two weeks and current hip pain rated as at least one out of 10 (on a 0-10 NRS) on the day of assessment’. This amendment was approved by the DMC and Research Ethics Committee (REC). Forty-eight participants had been recruited at the time of this amendment.

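### The primary model adjusts for one baseline pain score expected to correlate only 0.2 with outcome; adding baseline WOMAC pain, already collected, would gain precision at almost no cost

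*Protocol article*

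**What the plan says.** **Entry.** Under Inclusion criteria, hip pain must score at least 4 on a 0–10 scale "on average over the last 2 weeks and current hip pain rated as at least 1 out of 10" on the day. Table 1 shows that the cut-off of 4 formerly applied to the day of assessment. The reason given for the change reads: "due to the day-to day variability of osteoarthritis symptoms, a number of potential participants did not meet the eligibility criterion of pain of 4/10" (meaning the same-day rule). Progress of the trial adds: "Forty-eight participants had been recruited at the time of this amendment".

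**Outcome.** Under Primary outcome measure, the score is a 0–10 "Pain Numeric Rating Scale for current hip pain (hip pain today"). The only pain NRS row in Table 2, at baseline and at every follow-up, is "Pain - Numerical Rating Scale score for current pain". WOMAC is also scheduled at baseline and at 2, 4 and 6 months. Table 2 labels that row as function, but the list of secondary outcomes says that WOMAC covers pain and stiffness too.

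**Model.** Under Statistical methods: "The primary analyses will be adjusted for the following baseline covariates: pain score, age and gender". Neither mention of the pain covariate gives its recall period.

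**Sample size.** The calculation uses "postulated correlations of 0.5 for repeat-measures and 0.2 for baseline-outcome", four follow-ups, an SD of about 2.5 and a target difference of 1 point, and arrives at 68 per arm for 80% power with 15% loss.

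**The concern.** Since the amendment each participant has two pain ratings around entry: a 2-week average, on which severity is now screened, and the rating for the day. The model was not revisited. It carries one pain score, not named exactly, and most naturally the same-day one.

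Two features make that covariate a modest one. The plan itself expects a correlation of only 0.2 with the outcome. And the same-day score is cut off at 4 in the participants recruited before the change and at 1 in those recruited after it; the first group is 48/204, or 24% of the planned total. A second baseline measure of pain is already in the questionnaire, but the primary model does not use it.

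What is at stake is precision. It matters because the planned power was lowered from 90% to 80% when the sample size was revised after poor recruitment, so there is little slack.

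**Working it through.** **Inputs from the protocol (Sample size):** difference 1, SD 2.5, four follow-ups, repeat-measures correlation 0.5, baseline-outcome correlation 0.2, two-sided 5%, power 80%, loss 15%.

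**Step 1: reproduce the plan's figure.** The variance of the mean of four follow-ups, relative to the variance of one score, is (1 + 3 × 0.5)/4 = 0.625. Adjusting for a baseline score with correlation 0.2 gives 0.625 − 0.2² = 0.585.

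Evaluable per arm = 2 × (1.96 + 0.84)² × 2.5² × 0.585 / 1² = 57.4, so 58. After loss, 57.4/0.85 = 67.5, so 68 (69 if 58 is rounded up first). The stated 68 reproduces. Power at 58 evaluable per arm is 80.4%.

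**Step 2: what the planned pain covariate gains.** Without it the factor is 0.625, which needs 62 evaluable per arm and gives 77.8% power at 58. With it the figures are 58 and 80.4%. The covariate removes 0.04/0.625 = 6.4% of the variance of the average.

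**Step 3: add baseline WOMAC pain.** Let c be its correlation with follow-up pain and k its correlation with the baseline NRS. The protocol gives neither. I assume c = 0.2 to 0.4 and k = 0.4. The share explained by both covariates is

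(0.2² + c² − 2 × k × 0.2 × c)/(1 − k²)

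and the new factor is 0.625 minus that share.

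| c (k = 0.4) | Share explained | Factor | Change from 0.585 | Power at 58 per arm |
|---|---|---|---|---|
| NRS only | 0.040 | 0.585 | – | 80.4% |
| 0.2 | 0.057 | 0.568 | −3% | 81.6% |
| 0.3 | 0.098 | 0.527 | −10% | 84.3% |
| 0.4 | 0.162 | 0.463 | −21% | 88.6% |

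Power is Φ(1/SE − 1.96) with SE = 2.5 × √factor × √(2/58). For c = 0.3, SE = 0.337 and 1/SE = 2.966, so Φ(1.006) = 84.3%.

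**Step 4: sensitivity to k.** With k = 0.6, c = 0.2 gives a factor of 0.575 (−2%) and c = 0.3 gives 0.534 (−9%).

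**Step 5: sensitivity to the 0.2.** If the same-day NRS in fact correlated 0.4 with outcome, its own factor would be 0.625 − 0.16 = 0.465. WOMAC with c = 0.2 and k = 0.4 would then add almost nothing: (0.16 + 0.04 − 0.064)/0.84 = 0.162 against 0.160. With c = 0.4 the share would be (0.16 + 0.16 − 0.128)/0.84 = 0.229 and the factor 0.396, which is 15% less variance.

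**The case against.** The strongest reply is that nothing is broken and an extra covariate is a matter of taste. Much of that stands. The sample size reproduces, the endpoint averages four assessments, and day-to-day variation is already inside the SD of 2.5 and the repeat correlation of 0.5. The 0.2 is a planning input, not an observation. Lowering the same-day floor from 4 to 1 widens the baseline spread and may raise the true correlation, which would shrink the gain (Step 5). The correlations for WOMAC are assumed, and at the low end the gain is about one point of power. The protocol gives no recall period for WOMAC, so it should be called a second baseline pain measure and not a measure of usual pain.

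The reply does not remove the point. The protocol itself fixes the covariate list, the extra score is scheduled for everyone, and adding it costs almost nothing.

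A reader might infer four stronger things, and the document supports none of them:

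- **That someone entering at 1/10 can show at most 1 point of benefit.** The model compares follow-up levels between arms, adjusted for baseline; it does not analyse change. A person with higher usual pain who enters on a good day will tend to score higher later in any arm, which leaves room for a difference between arms.
- **That the mismatch between entry and outcome biases the comparison.** Both arms enter under the same rule and are scored on the same item.
- **That the sponsor found same-day pain unfit as an outcome.** The amendment says only that candidates missed a threshold on the day.
- **That the 2-week score is discarded.** It has to be obtained at screening, where a form is completed, and the undefined symptom-severity subgroup could use it. The accurate statement is that the primary model does not name it.

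**Conclusion.** The point holds as an improvement in precision and clarity, not as an error of validity. The protocol leaves the recall period of its pain covariate unstated after an amendment that created two candidates. On the natural reading, it relies on a score from which it expects little, and leaves a second baseline pain score out of the primary model.

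The likely gain is 3% to 21% of variance, or about 1 to 8 points of power at the planned size. It rests on WOMAC pain correlating 0.2 to 0.4 with follow-up pain and 0.4 with the baseline NRS, on the plan's own 0.2 and 0.5, and on equal correlation with each follow-up. It would be smaller if WOMAC overlapped more with the NRS, or if the same-day NRS predicted better than planned.

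**What to change.** Before unblinding:

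1. State that the pain covariate is the baseline current-pain NRS.
2. Add the baseline WOMAC pain score to the fixed covariates of the primary model, beside baseline NRS, age and gender.
3. Use the 2-week average NRS from screening only in a supportive analysis of participants enrolled after the amendment. The 48 recruited before it were not screened on that score, so it cannot serve everyone in the primary model.

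The primary outcome, sample size and data collection stay as they are. The cost is one degree of freedom and a short change to the analysis text.

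A matching 2-week item on the follow-up questionnaires is not worth adding. Recruitment began in January 2016 and runs 29 months, to about mid-2018, while the protocol version described is dated 3 April 2018. A new question would reach only the last participants' later visits.
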